### Sample size

A power analysis was used to calculate the sample size for this study. We adopted usability as our primary outcome measure. To determine the effect size for our study, we referred to the Overall Acceptability Score [34], where the intervention group scored 45.2 (2.9) and the control group scored 40.4 (1.3). To account for potential differences in our local sample, which may consist of older individuals with lower mobile device literacy, we used a conservative approach and discounted the effect size by one-third for sample size calculation (which was 0.72). This was done to ensure an adequate sample size.

Assuming an alpha value of 0.05, a power of 80%, and an effect size of 0.72 [33], the sample size for each group should be 32. Accounting for a 10% drop-out rate, the total sample size in this study will be 70 (i.e., 35 per group).

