#### Preliminary effectiveness

The preliminary effectiveness outcomes are comprised of quality of life, utilization of health services, sustained use intention, and rate of adherence.

Quality of life will be evaluated using the Hong Kong version of the 5-level EuroQol 5-dimension scale (EQ-5D-5L), a validated descriptive system that has been used extensively in different jurisdictions. It consists of five dimensions: mobility, self-care, usual activities, pain or discomfort, and anxiety or depression. Each dimension has five levels of severity, namely, no problem, slight problem, moderate problem, severe problem, and extreme problem [27,28].

Utilization of health services will be measured by the number of attendances at a general practitioner’s office, emergency department, hospital, and general out-patient clinic. The data will be self-reported by subjects with confirmation via medical and attendance certificates [23].

The subjective primary outcome, sustained use intention, will be measured using a three-item, 5-point Likert scale measurement tool [29,30]. The scale ranges from 1 = strongly agree to 5 = strongly disagree. Lower scores indicate a higher chance of using the WMD sustainably.

The objective primary outcome, rate of adherence, will be evaluated by examining the number of days and the average length of time per day that the subject has worn the device. The data will be logged automatically into the system when the subject starts wearing the device.

Background demographics such as age, gender, marital status, educational level, primary caregiver, frequency of caretaking support, experience of using wearable monitoring devices, and eHealth literacy, will be collected at the baseline to account for differences between the groups.

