### Data analysis

Statistical tests will be performed using the software, Statistical Package for Social Sciences (SPSS) version 26. Descriptive analyses will be used to present the baseline demographic data. The differences and changes in outcomes for the quantitative data will be estimated using the Generalized Estimating Equation (GEE). For each outcome, (1) the between the intervention and control group (between-group) effects, (2) the within-group (time) effects, and (3) the group-by-time interaction (group X time) effects will be investigated. However, it is important to note that the validity of the GEE analysis relies on the assumption that data are missing completely at random (MCAR) [31]. Therefore, we will employ Little’s test to assess whether the missing data in our dataset are MCAR. If the test results are significant or indicate non-MCAR data, we will utilize Weighted Generalized Estimating Equation (WGEE) to analyze the outcome measures instead. Intention-to-treat will be our primary choice to analyze the data [32]. The level of significance will be set at p < .05 for a two-tailed test.

The qualitative data from the semi-structured interviews will be examined using the principles of deductive thematic analysis [33]. All focus group interviews will be conducted with audio recordings. Transcription and translation will be performed manually by research team members. To enhance conformability, an audit trail will be maintained to resolve any differences through agreement.

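### The sample size section and the outcome section name different primary outcomes, and the stated 80% power is tied to no endpoint that the trial defines

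*Protocol article*

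**What the plan says.** Two sections of the protocol article assign the primary label differently.

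- **Sample size:** "We adopted usability as our primary outcome measure". For the effect size the authors write "To determine the effect size for our study, we referred to the Overall Acceptability Score", from a cited study with means (SDs) of 45.2 (2.9) and 40.4 (1.3). They discount the effect to 0.72. With alpha 0.05 and 80% power they obtain 32 per group, and 70 in total after a 10% drop-out allowance.
- **Preliminary effectiveness:** "The subjective primary outcome, sustained use intention, will be measured using a three-item, 5-point Likert scale measurement tool". The next paragraph adds: "The objective primary outcome, rate of adherence, will be evaluated by examining the number of days and the average length of time per day". Both metrics refer to device wear.

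The Usability section describes six constructs of the senior technology acceptance model (STAM): attitude, usefulness, ease of use, self-efficacy, anxiety and facilitating conditions. Each is rated from 1 to 10, and anxiety runs in the opposite direction to the rest. Focus group feedback covers the remainder. No total score is named, and the Overall Acceptability Score appears in none of the outcome sections.

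The Data analysis section examines group, time and group-by-time effects for every outcome and adds: "The level of significance will be set at p < .05 for a two-tailed test".

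**The concern.** Usability, sustained use intention and adherence are separate outcomes in this article. Usability falls under the first objective and the other two under the third. A reader cannot tell which of them decides whether the programme worked, so any of the three could later be reported as the primary result.

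The power statement does not settle the matter. It rests on a score that the trial does not list, and it is offered for a domain that has several constructs and no named total. A null result on intention or adherence could not be judged against the stated 80%. A positive result on one of three candidates would carry more false-positive risk than the nominal 5% suggests.

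**Working it through.** **1. Reproduce the plan's figure.** Inputs from Sample size and Data analysis: d = 0.72, two-sided alpha 0.05, power 80%, equal groups.

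- Normal approximation: n = 2(1.960 + 0.842)² / 0.72² = 15.70 / 0.518 = 30.3, so 31 per group.
- Two-sample t-test: n = 31.27, so 32 per group, with actual power 80.9%. This matches the plan.
- Drop-out: 32 × 1.10 = 35.2, about 35 per group (70 in total). Dividing instead, 32 / 0.90 = 35.6 gives 36 per group (72 in total). The stated 70 is within rounding convention.

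**2. Trace the effect size.** Pooled SD = √[(2.9² + 1.3²)/2] = 2.247, and d = (45.2 − 40.4)/2.247 = 2.14. One third of this is 0.71, close to the 0.72 used. The text describes a discount by one third, which would give 2.14 × 2/3 = 1.42. That mismatch is a separate matter, and the value used is the more cautious one. What matters here is that 0.72 comes only from the Overall Acceptability Score. The article gives no expected effect for sustained use intention, for either adherence metric or for any STAM construct.

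**3. Compare the labels.**

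| Outcome | Called primary in | Single score named? | Effect size given? |
|---|---|---|---|
| Usability | Sample size | No: six constructs plus focus groups | Only from another score |
| Sustained use intention | Preliminary effectiveness | Three-item scale | No |
| Rate of adherence | Preliminary effectiveness | No: two metrics | No |

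**4. False-positive risk.** Allow one test at 0.05 per named primary and assume independence:

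- two primaries (intention, adherence): 1 − 0.95² = 9.75%
- three primaries: 1 − 0.95³ = 14.3%

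Positive correlation between the outcomes lowers both figures.

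**5. What 32 per arm can detect.** For a two-sample t-test at two-sided 0.05, the difference detectable with 80% power is 0.711 SD at 32 per arm. It is 0.717 at 31.5 per arm (35 × 0.90). Because no effect is given for intention or adherence, the range below is assumed:

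| True standardised difference (assumed) | Power at 32 per arm |
|---|---|
| 0.3 | 22% |
| 0.4 | 35% |
| 0.5 | 50% |
| 0.6 | 66% |
| 0.72 | 81% |

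**The case against.** The best defence has four parts.

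- **The labels may be local.** The two primaries sit under a preliminary heading and could mean primary within that domain. The text does not say so, and the article claims 80% power without limiting it to a domain. The contradiction stands.
- **Borrowing a standardised effect is ordinary practice.** This is right, and the arithmetic is correct. The fault is narrower: the borrowed effect is not linked to any variable that this trial defines.
- **Multiplicity rules and STAM scoring may be in documents not shown.** This is also fair. The absence of a testing order is not counted as an error here, and naming no total is not proof that none exists. But no analysis plan can make both printed statements of the primary outcome true.
- **Usability could legitimately be primary.** It is the first objective. The documents conflict without settling which outcome should prevail, so the choice is the sponsor's.

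A reader might infer that no stated error rate applies to the trial at all. That goes too far, because a two-tailed 5% level is stated and holds for any single test. A reader might also count every adherence metric, STAM construct and model effect, and reach 26% (1 − 0.95⁶) or 60% (1 − 0.95¹⁸). Those counts go beyond the three outcomes that the article calls primary. Nor can power be said to have fallen to about 71%: that figure presumes a Bonferroni split between two primaries, which the article does not adopt.

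**Conclusion.** The point holds. The article contradicts itself on its primary outcome, and its power calculation, though numerically correct, attaches to no defined endpoint of the trial. With one unadjusted test for each of the three named primaries, the chance of at least one false positive is up to 14.3% under independence. It is 9.75% if only the two under Preliminary effectiveness count. Correlation between outcomes makes both smaller.

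Power for intention or adherence is unknown rather than shown to be low. It would be about 81% if the true standardised difference were 0.72 and about 50% if it were 0.5, and the documents support neither value for those outcomes. The conclusion rests only on the printed labels and the printed source of the effect size, not on anything that an article might leave to a fuller document.

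**What to change.** Name one primary outcome with one metric, one time point and one contrast, and use the same label under Preliminary effectiveness and Sample size.

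A natural candidate is device-logged days worn, compared between arms at T3 (6 months). It matches the stated aim of sustained daily use, T3 is the time point meant to show lasting effect, and the data are logged rather than self-reported. The period over which days are counted should be stated. Average time worn per day, sustained use intention and the STAM constructs would then be secondary. If the sponsor prefers another primary, or keeps more than one, the same precision is needed, with a fixed testing sequence or an alpha split for several primaries.

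Restate the power for the chosen endpoint as a detectable difference, not an expected effect. For a single between-arm comparison: about 32 analysed per arm gives 80% power to detect a standardised difference of about 0.71 to 0.72 at two-sided 0.05, and about 50% if the true difference is 0.5 (assumed). The 0.72 should not be carried over as the expected effect on adherence, because nothing in the article supports it.

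The cost is a protocol amendment, best made before any between-arm results are seen, and possibly an aligned registry entry. A single primary at 0.05 needs no extra participants or data for this restated power. The sponsor gives up the option of claiming success on whichever candidate proves significant.

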### Ethical considerations

The study was approved by the Ethics Committee of the Hong Kong Polytechnic University (HSEARS20220429001). An information sheet and consent form will be given to the potential subjects during the recruitment process. A thorough explanation of the study will be given to ensure that the subjects are all well informed before their written informed consent is collected. Participation is completely voluntary, and they reserve the right to drop out at any time during the study. Only subjects who have signed the written consent form will be included in the study.

## Discussion

Amidst the COVID-19 pandemic and the implementation of preventive measures, the advancement, popularity, and acceptance of health technologies accelerated, particularly among community-dwelling older adults [35,36]. WMDs allow healthcare professionals to remotely monitor the health of community-dwelling older adults and provide immediate support when necessary. Despite their advantages, the evidence suggests that older adults tend to use WMDs only for a short period of time. Therefore, it is paramount to develop innovative approaches to enhance the motivation of older adults to use WMDs sustainably, so that the benefits of using them can be realized.

We have designed a novel approach that includes community health workers to enhance the sustainability of using WMDs among community-dwelling older adults. To the best of our knowledge, the proposed study is the first randomized controlled trial to evaluate the sustainability and effectiveness of WMDs with an additional intervention that includes community health workers as peer supporters. The study utilizes commercially available WMDs, which increases the real-world practicality of the study. In addition, the assessment tools adopted from prior empirical studies have been validated, increasing the reliability of the study. The control group, which does not involve CHWs, allows for a comparison to be made and provides insight into the significance of peer support. If successful, this study will generate evidence on interventions involving CHWs to enhance the long-term use of WMD in promoting the health of community-dwelling older adults. Moreover, by utilizing WMD technology and expanding the role of community health workers, the suggested intervention could overcome the geographic challenges to implementing community healthcare and become a cost-effective addition to ease the shortage of healthcare professionals.

Some limitations are anticipated. First, since the study will recruit members from five local community centers onsite, the potential subjects might be more socially active than those who do not often join activities organized by community centers, which could introduce a selection bias that could affect the results; therefore, the findings of this study need to be carefully examined. Second, the study was conducted with a group of Chinese-speaking older adults. Previous studies have shown differences between cultures in the adoption of WMD. The Chinese population is inclined to be more socially influenced to adopt the use of WMD compared to their Swiss counterparts [37]. Therefore, the peer support effect might be more profound in the Chinese culture than in some other cultures.

## Conclusion

Wearable monitoring devices (WMD), such as smartwatches, have shown promising health benefits, but maintaining long-term use among older adults remains a challenge. This article proposes a randomized controlled trial protocol that involves community health workers as peer supporters to increase the sustainability of using WMDs among community-dwelling older adults. If proven successful, older adults can enjoy the health benefits arising from the use of the WMD and be able to live independently in the community for longer than might overwise have been the case.
